### Exclusion criteria

Babies born <36 weeks gestation, <2500 g birth weight, those admitted to the neonatal intensive care unit (NICU) for >3 days and those with severe congenital anomaly will be excluded. Mothers with a previous unexplained sudden infant death, who have severe mental health problems (as determined by contact with mental health services) or who are involved in a methadone maintenance programme will also be excluded.

### Randomisation

Mothers agreeing to participate will be randomised to one of the two groups. Allocation will be concealed and performed, following application of inclusion/exclusion criteria and consent to participate in the study, by opening a sealed envelope opened in numbered sequence. As level of deprivation and parity may significantly affect the primary outcomes, stratified block allocations will be used employing a block size of 3 within each strata combination. Deprivation quintile (derived from home address) of less than 3 versus 3 or more, and parity of 1 versus 2 or more will be used.

After allocation, participant blinding will not be possible. However, the analysis of all overnight studies will, where possible, be performed blind to group allocation. Any measures of parenting that are recorded by audio, will then be analysed blind to group allocation.

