**Methods/Design:**

This two arm randomised controlled trial is being conducted with 200 mother-baby dyads recruited from Māori communities in areas of high deprivation in the Hawkes Bay, New Zealand. They are randomised to *wahakura* or bassinet use and investigation includes questionnaires at baseline (pregnancy), when baby is 1, 3, and 6 months, and an overnight video sleep study at 1 month with monitoring of baby temperature and oxygen saturation, and measurement of baby urinary cotinine and maternal salivary oxytocin. Outcome measures are amount of time head covered, amount of time in thermal comfort zone, number of hypoxic events, amount of time in the assigned sleep device, amount of time breastfeeding, number of parental (non-feed related) touching infant events, amount of time in the prone sleep position, the number of behavioural arousals and the amount of time infant is awake overnight. Survey data will compare breastfeeding patterns at 1, 3, and 6 months as well as data on maternal mind-mindedness, maternal wellbeing, attachment to baby, and maternal sleep patterns.

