### Drop-out rate

After discussion with the midwifery group within which we will work, we estimate dropout of 5% at 1 month, 20% at 3 months, and 25% at 6 months. Our power studies are mainly dependent on the 1 month measures, so we will increase our required numbers by 5%.

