### Total numbers required

Overall, we believe that we should aim to recruit enough babies so that we have complete data at 1 month, of 100 babies per group – i.e. enrol 105 babies per group.

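### A block size of 3 with two arms makes every completed block 2:1 or 1:2, so the stratified blocks do not secure the equal allocation behind 105 per group

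*Protocol article*

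**What the plan says.** Under Randomisation, the protocol article says "Mothers agreeing to participate will be randomised to one of the two groups" and that "stratified block allocations will be used employing a block size of 3 within each strata combination". There are two binary stratifiers, so four strata: "Deprivation quintile (derived from home address) of less than 3 versus 3 or more, and parity of 1 versus 2 or more will be used". The reason given for stratifying is that both factors may affect the primary outcomes. Participants and recruitment adds only that randomisation is in blocks by these two factors.

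The sample size sections work with equal groups throughout: 88 per group for head covering, 98 for thermal comfort and 106 for breastfeeding. Total numbers required aims for "complete data at 1 month, of 100 babies per group" and concludes "i.e. enrol 105 babies per group".

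The article gives no unequal ratio. It also does not say how a block of 3 is divided, whether block types are mixed, or whether 3 counts participants per arm.

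**The concern.** Permuted blocks within strata are used to keep the arms close to equal as recruitment proceeds, both overall and within each stratum. With two arms at 1:1 this needs an even block size, because only then does every completed block return the difference to zero. A block of 3 always leaves a difference of one.

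Two things are at stake. First, the allocation ratio is not determined by the text, although every sample size assumes equal groups. Second, parity and deprivation were made stratifiers because they may affect outcome, yet the stated procedure puts no tight bound on imbalance within a stratum. The Data analysis section names chi-squared and t-tests for the group comparisons, so the article relies on the allocation for balance on these factors.

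This is not a detail left to a fuller document. The article does give a block size, and that size does not fit its own design.

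**Working it through.** **Inputs.** Two arms, block size 3 and four strata (Randomisation). 100 evaluable and 105 enrolled per group, 210 in total (Total numbers required). 5% inflation for dropout at 1 month (Drop-out rate). Thermal comfort in 75% of cot sleepers with a 20-point difference (Temperature control). Breastfeeding 45% v 65% (Breastfeeding, under Sample size). Assumed: two-sided 5% tests, and thermal comfort falling from 75% to 55%.

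**The plan's own figures.** 100 × 1.05 = 105 per group. The standard two-proportion formula with equal groups and continuity correction gives:
- Breastfeeding: n = [1.960·√(2 × 0.55 × 0.45) + 0.842·√(0.45 × 0.55 + 0.65 × 0.35)]² / 0.20² = 96, and 106 after correction, as stated.
- Thermal comfort: 89, and 98 after correction, as stated.
- Head covering, 3% v 18%: 65, or 78 after correction, so the stated 88 is not reproduced. That is a separate matter.

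The two exact matches confirm that the plan assumes 1:1 allocation.

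**Blocks of 3.** 210 / 3 = 70 blocks, ignoring incomplete last blocks in the four strata. Each block contributes +1 or −1 to the arm difference d.

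*Reading A: 2:1 and 1:2 blocks mixed at random.* Then d = 2·Binomial(70, 0.5) − 70.
- The mean is 0, so the expected split is 105:105. It is reached exactly (35 blocks of each type) with probability 0.095.
- SD = √70 = 8.4, and the mean absolute difference is 6.7.
- P(|d| ≥ 10) = 0.28, P(|d| ≥ 16) = 0.07 and P(|d| ≥ 20) = 0.022.
- Simple randomisation of 210 would give SD √210 = 14.5.
- Variance of a difference relative to 105:105: for 100 v 110, (1/100 + 1/110)/(2/105) = 1.002; for 97 v 113, 1.006.
- Power with 200 evaluable (no continuity correction), 100:100 against 92:108: thermal comfort 84.8% against 84.5–84.7%; breastfeeding 81.6% against 81.3–81.4%.
- Within a stratum, an odd number of completed blocks cannot balance. As an illustration (stratum sizes are not given), 30 mothers make 10 blocks, and P(|d| ≥ 4) = 2 × (1 + 10 + 45 + 120)/1024 = 0.34.

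*Reading B: every block leans the same way.* The split is 140:70.
- Variance ratio: (1/140 + 1/70)/(2/105) = 1.125.
- Equivalent equal group size: 2 × 140 × 70/210 = 93.3 per group.
- Power with 200 evaluable, 100:100 against 2:1 (the range covers which arm is larger):

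| Outcome | 100:100 | 2:1 |
|---|---|---|
| Head covering, 3% v 18% | 93.9% | 90.3–92.3% |
| Thermal comfort, 75% v 55% | 84.8% | 79.8–81.2% |
| Breastfeeding, 45% v 65% | 81.6% | 76.8–77.3% |

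*Reading C: 3 means three per arm.* The block size is 6, every completed block is balanced, and only the text is wrong.

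**Even blocks for comparison.** The difference in a stratum never exceeds half a block: 2 for size 4, 3 for size 6. Over four strata the total is at most 4 × 2 = 8 or 4 × 3 = 12.

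**The case against.** The strongest reply is that little is lost in practice. With block types mixed at random, the expected ratio is 1:1, the variance of the imbalance is one third of that under simple randomisation (70/210), and the tests named in Data analysis do not need equal groups. Splits such as 97 v 113 raise the variance by only 0.6%. The sentence may also be a slip for three per arm. All of this stands, and it limits the size of the point.

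Two stronger readings are tempting, and the article supports neither. A reader might infer that blocks of 3 make equal allocation impossible or defeat the stratification altogether. They do not: 105:105 remains attainable, and balance on parity and deprivation is still better than without blocking, though looser than with even blocks. A reader might also infer that the trial randomises 2:1 and is short of power. Nothing says that all blocks lean the same way, and the target of 105 per group points against it. The abstract's figure of 200 dyads gives no allocation ratio, so it settles nothing.

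What the reply does not remove is the conflict itself. A block of 3 and a plan for equal groups stand together with no rule connecting them, and no later analysis document can make a block of 3 balance.

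**Conclusion.** The point holds as a conflict between the stated block size and the equal-group design. Equal allocation, and tight balance within the four strata, are not secured; they are not prevented either.

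The probable cost is small: under random mixing, an SD of 8.4 in the arm difference and under half a point of power for a 92:108 split. The material loss (140 v 70, variance up 12.5%, breastfeeding power about 77% instead of about 82%) arises only if all blocks lean one way, which the text does not say.

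These figures rest on two-sided tests, 70 complete blocks, thermal comfort falling from 75% to 55%, and 200 evaluable babies. The last is the 1-month target. The article expects 20% dropout by 3 months, when breastfeeding is assessed, so the two breastfeeding powers show the effect of the split, not the power to expect at that visit.

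Because the actual block composition cannot be read from the article, the conclusion concerns what the stated rule secures, not how the trial was in fact allocated.

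**What to change.** In the Randomisation section, replace the block size of 3 with an even block size (for example 4 or 6, or a mix of even sizes) and state 1:1 allocation within each of the four strata. Apply this to all unopened envelopes. For mothers already randomised, report the block composition actually used, including whether 2:1 and 1:2 blocks were mixed and how. If 3 meant three per arm, no procedure changes: correct the text to a block size of 6.

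The only cost is regenerating the remaining allocation list and its envelopes. No extra participants or visits are needed, and the sample size does not change.

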### Contamination

There may be contamination with those assigned to one condition deciding to obtain and use the other type of sleeping device. We will check the degree of contamination by identifying this at the 1 month sleep study, and by asking at each time point about use of other sleep devices. For safety analyses (head covering, peripheral temperature and oxygen saturation), analysis will be by actual device used. For breast-feeding results, both the intention to treat and actual sleep device used will be analysed.

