### Smoking

Maternal smoking in pregnancy is recognised as the primary cause of increased vulnerability when bedsharing. A decreased arousability to hypoxia from fetal exposure to passive smoking may well be the mechanism that leads to this increased risk
[17–19]. To add to the complexity, bedsharing is also a common and valued childcare practice in many cultures, including Māori and Pacific families in New Zealand
[20] and is seen in many cultures as developing and maintaining a sense of ongoing connection to the infant
[21, 22] as well as facilitating breast feeding
[23–25]. Māori women however, have high rates of smoking and Māori women from communities of high deprivation in Auckland, New Zealand’s biggest city, have a prevalence of cigarette smoking in pregnancy of 53%
[26]. Despite vigorous efforts to decrease smoking in pregnancy
[27] there has been limited success
[28]. Likewise, efforts by health professionals, the Ministry of Health and coroners to discourage bedsharing do not appear to have had any impact as 65% of Māori mothers in Auckland bedshare with their infants for some part of the night
[26]. In addition, a mortality review of the years 2000 to 2009 in the same city showed that 64% of all SUDI cases were found dead in a shared bed
[29]. Nationally, 43% of SUDI deaths occurred when bedsharing
[3], and an increasing proportion of these deaths are now labelled accidental suffocation
[30]. Unfortunately, mortality review data collection around risk factors associated with these deaths is incomplete in New Zealand and it was not possible to identify the contribution of factors such as smoking in pregnancy or alcohol consumption on the night of death.

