## Methods/Design

### Overall study design

Ethical approval to conduct this study has been granted by the New Zealand Central Region Ethics Committee (CEN/10/12/054).

This is a randomised controlled trial of *wahakura* versus bassinet to test the following hypotheses:That the use of a *wahakura* is not significantly different in terms of thermal environment, head covered duration, episodes of oxygen desaturation, or total sleep duration, than infants sleeping in a separate bassinet in the same room.That the ‘*wahakura* group’ spends less time per night bedsharing on the same bed surface than the ‘bassinet group’.That the use of a *wahakura* is associated with significantly increased breastfeeding episodes, breastfeeding duration, and more parental “looking and touching” episodes.That use of a *wahakura* is associated with greater involvement of the extended family, more attention to other issues of safety, and a greater sense of connection to familyThat the use of the *wahakura* promotes maternal and extended family mind-mindedness and development of individual, family, and cultural identity.

Participants will be randomized to receive a *wahakura* or bassinet and the above aspects will be studied using a combination of questionnaires and an overnight sleep study with video, temperature and oxygen saturation measurement. Baby urine (for cotinine) and maternal saliva (for oxytocin) will be collected, and a recording will be made of mothers talking about their feelings about their baby.

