### Outcome measures

Primary outcome measures for the infant will be derived from the overnight sleep study (amount of time head covered, amount of time in thermal comfort zone, number of hypoxic events and amount of time in the sleep device) and from surveys (full or exclusive breastfeeding at 3 and 6 months). Secondary outcomes identified from the sleep study include number of infant head covering events, number of parental (non-feed related) touching infant events, amount of time in the prone sleep position, the number of behavioural arousals, and the amount of time infant is awake overnight.

Psychosocial factors will also be measured. Using questionnaires, maternal environmental chaos will be measured at baseline. Social support, and social and economic stress will be measured at baseline and 3 months. Maternal depression and change in depression (from baseline) will be measured at 3 months and 6 months. Parenting factors, including beliefs about infant care, attachment, and parenting adaptation will be measured at baseline and 3 months using both the questionnaires and maternal salivary oxytocin levels at baseline, 1 month and 3 months. Maternal mind-mindedness will be measured at baseline, 3 and 6 months, using the questionnaires, and an audio recording of the mother talking about her baby (see Table 
1).

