### Head covering

The proportion of babies having an overnight sleep with a head covering episode by blankets was 1/37 and so, in order to detect a difference of 15% between babies sleeping in wahakura and cots with 80% power using the 5% level of significance, two groups of 88 babies would be needed.

Assuming the proportion of babies having an overnight sleep with a head-covering episode by blankets will be 3% when sleeping in a bassinette, 88 babies per group are required to detect a difference of 15% between babies sleeping in wahakura and cots with 80% power using the 5% level of significance.

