### Temperature control

From our previous study
[49], we estimated that 32% of bedsharing babies and 3.5% of cot sleeping babies had a core-peripheral temperature difference of <1°C after they had been asleep for 3.5 hours, suggesting thermal stress from a warm environment. About 40 babies per group are needed detect a difference of this magnitude with 90% power using the 5% level of significance. Ideally, babies should be neither too hot nor too cold; 75% of the cot-sleeping babies were in the ideal comfort zone, where the peripheral temperature is between -1°C and -3°C of the core temperature. Two groups of 98 babies have the potential to detect a difference of 20% with 80% power using the 5% level of significance.

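### The safety analysis by device used has no category for sleep directly on the adult bed, so whole-night outcomes can mix adult-bed exposure into both device groups and shrink a true difference

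*Protocol article*

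**What the plan says.** Under Contamination, the protocol article describes the problem as "those assigned to one condition deciding to obtain and use the other type of sleeping device". It then sets the rule: "For safety analyses (head covering, peripheral temperature and oxygen saturation), analysis will be by actual device used". For breastfeeding, both the randomised and the actual-use comparison are promised. For safety, only the actual-use comparison is named there.

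Under Outcome measures, the primary outcomes from the overnight study are "amount of time head covered, amount of time in thermal comfort zone, number of hypoxic events and amount of time in the sleep device". The first three are whole-night quantities for each baby, and time in the device is a separate outcome. The Head covering paragraph of the sample size likewise counts babies with an episode during an overnight sleep.

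Under Overall study design, hypothesis 1 is that wahakura use "is not significantly different in terms of thermal environment, head covered duration, episodes of oxygen desaturation, or total sleep duration", compared with sleeping in a separate bassinet. Hypothesis 2 is that the wahakura group "spends less time per night bedsharing on the same bed surface than the" bassinet group. The Safe sleep instructions also treat bedsharing without a protective device as a distinct situation.

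Under Data analysis, the data are analysed by modified intention to treat, with an additional per-protocol analysis. No exception is made there for safety.

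**The concern.** There are three places a baby may sleep on the study night: in the wahakura (including when it lies on the shared bed), in the bassinet, or directly on the adult sleep surface. The rule names only the first two. A baby who spends three hours in the bassinet and five directly on the adult bed has used one device, but the night's covered time, temperature and desaturations come from two places. A baby who spends the whole night on the adult bed has used neither device, and the rule does not say where that baby goes.

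This is separate from the loss of randomisation in any actual-use analysis. The mixing would remain even if device use were random.

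The stake is the direction of the error. Safety is framed as the absence of a significant difference, and the Discussion says the trial will inform whether the wahakura can be recommended. Anything that dilutes the contrast between devices makes that conclusion easier to reach.

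**Working it through.** **Inputs from the protocol article.** Temperature control: "we estimated that 32% of bedsharing babies and 3.5% of cot sleeping babies had a core-peripheral temperature difference of <1°C", measured after 3.5 hours asleep. So the bassinet rate is taken as b = 3.5% (the cot figure) and the direct-bed rate as d = 32%. Total numbers required: 100 babies per group with complete 1-month data.

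**Assumed inputs (not in the documents).** The true in-wahakura rate w (15%, with 10% and 20% as a range). The shares fB and fW of bassinet-labelled and wahakura-labelled babies whose night takes the full adult-bed risk. If a baby takes only half of the excess risk, halve the share. The test is taken as two-sided at 5%.

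**The plan's own figure.** About 40 per group for 32% v 3.5% at 90% power. The normal approximation with pooled variance gives [1.96√(2 × 0.1775 × 0.8225) + 1.2816√(0.035 × 0.965 + 0.32 × 0.68)]² / 0.285² = 36. With continuity correction it is 43. The stated figure lies between them, so these rates are used as the plan uses them.

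**Mixing.** The labelled rates are

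- bassinet: b + fB(d − b)
- wahakura: w + fW(d − w)

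The observed difference is (w − b) − [fB(d − b) − fW(d − w)]. With equal shares f it reduces to (1 − f)(w − b).

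**Direction.** If d > w > b, then d − b exceeds d − w, so the bracket is positive whenever fB is at least fW and above zero, and the excess shrinks. With w = 15% it shrinks as long as fW/fB is below 28.5/17 = 1.68. Above that ratio the excess is overstated: with fB = 20% and fW = 40% the rates are 9.2% and 21.8%, a difference of 12.6 points against a true 11.5.

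**Size at w = 15%.** Power = Φ[(difference − 1.96 × SE0)/SE1], with SE0 from the pooled rate and SE1 from the separate rates, n = 100 per group.

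- No adult-bed share: 15.0 − 3.5 = 11.5 points; (0.115 − 1.96 × 0.0410)/0.0402 = 0.86; power 81%.
- 20% in both: bassinet 3.5 + 0.2 × 28.5 = 9.2%; wahakura 15 + 0.2 × 17 = 18.4%; 9.2 points; (0.092 − 1.96 × 0.0488)/0.0483 = −0.07; power 47%.
- 40% bassinet, 20% wahakura: 14.9% and 18.4%; 3.5 points; (0.035 − 1.96 × 0.0527)/0.0526 = −1.30; power 10%.

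**Range over the assumed wahakura rate** (difference in points, power):

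| w | No share | 20% in both | 40% in both | 40% bassinet, 20% wahakura |
|---|---|---|---|---|
| 10% | 6.5, 45% | 5.2, 21% | 3.9, 11% | −0.5, sign reversed |
| 15% | 11.5, 81% | 9.2, 47% | 6.9, 24% | 3.5, 10% |
| 20% | 16.5, 96% | 13.2, 73% | 9.9, 42% | 7.5, 27% |

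The Background figure that "65% of Māori mothers in Auckland bedshare with their infants for some part of the night" shows that direct bedsharing is unlikely to be rare. It is not used as a share: it covers any part of the night, in another city, among mothers not given these devices.

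**The case against.** The strongest reply is that the protocol never says adult-bed events are scored to a device. The wording could mean attribution by time segment, a separate no-device group, or exclusion. Hypothesis 1 describes the comparator as sleeping in a bassinet, and the Sleep studies section synchronises video with oximetry and temperature and looks for behaviour linked to hypoxic or temperature events. The per-protocol analysis might remove mixed nights. A condensed article may also leave such definitions to the analysis plan.

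Much of this stands. A reader might infer that adult-bed events are counted as bassinet events, that babies in neither device are dropped, and that the wahakura is therefore made to look safe. The documents state none of these. The rule would charge adult-bed time to the wahakura as well as to the bassinet, and how far the bassinet is affected more depends on hypothesis 2, which is under test.

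The size is also weakly anchored. The wahakura rate and the shares are assumed. The only documented direct-bed rate is for heat, as a core-peripheral difference at 3.5 hours; the Sleep studies section instead defines heat stress by a peripheral temperature threshold. No direct-bed rate is given for head covering or desaturation. For head covering, the sample size gives only the bassinet side: "Assuming the proportion of babies having an overnight sleep with a head-covering episode by blankets will be 3% when sleeping in a bassinette".

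Two things are not answered. The article does more than stay silent: it fixes an analysis rule with two categories for a trial with three sleep places. And the analyses that might help do not settle it: per-protocol compliance is undefined for part-night use, and modified intention to treat for all data is not reconciled with an actual-use rule for safety.

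**Conclusion.** The point holds as a badly fixed rule, not as a stated misattribution. A per-baby device label on whole-night outcomes is the plain combination of the Contamination and Outcome measures sections, and it mixes adult-bed exposure into both device groups.

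The bias is towards no difference on two conditions: the adult-bed rate exceeds both device rates, and direct bedsharing is no commoner in the wahakura group. The shrinkage is greater if hypothesis 2 is true. It does not depend on hypothesis 2, because equal shares already shrink the excess by the factor 1 − f. If direct bedsharing were much commoner with the wahakura, the error would run the other way.

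The power losses in the working show that modest mixing could matter at the planned sample size. They are not estimates of what will happen, and they apply to heat stress only. The plan should be changed, because the device comparison is the trial's main safety evidence and the data for a better analysis are already collected.

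**What to change.** In the Contamination section, state that the actual-use safety analysis attributes time and events to one of three states: in the wahakura, in the bassinet, or directly on the adult sleep surface. Use the coded and synchronised video to assign the state. Express head-covered time, time outside the comfort zone and hypoxic events per hour in that state. Report direct bedsharing as its own category, so that babies who used neither device are kept. Compare wahakura with bassinet on in-device time.

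Also state that whole-night safety totals will be reported by randomised group. This reconciles the Contamination rule with the modified intention to treat under Data analysis.

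The cost is analysis wording. Infant location has to be coded anyway to obtain time in the device, and the signals are already synchronised, so no new measurement is needed. The downside is fewer hours per state and a non-randomised comparison. The by-state analysis therefore supports the as-randomised result and does not replace it.

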#### Data analysis

The data will be analysed using modified intention to treat, including only those who completed at least one of the 1, 3 or 6 month visits. Chi-squared tests or Student t-tests will be used to compare the outcomes in the two groups. A per protocol analysis will also be carried out to estimate differences in the outcome variables in those who were compliant with the sleeping arrangement to which they were assigned.

This study will also provide an opportunity to examine factors associated with breastfeeding and sleep practices in a disadvantaged group. The breastfeeding data will be analysed using a discrete time model.

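### The primary safety outcomes are given two analysis bases, and the by-device-used comparison is planned without the deprivation and parity factors the plan calls prognostic

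*Protocol article*

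**What the plan says.** The Contamination section expects switching by choice: "There may be contamination with those assigned to one condition deciding to obtain and use the other type of sleeping device". It then sets a rule for safety, "For safety analyses (head covering, peripheral temperature and oxygen saturation), analysis will be by actual device used", and a different one for breastfeeding: "For breast-feeding results, both the intention to treat and actual sleep device used will be analysed".

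The Data analysis section gives a general rule: "The data will be analysed using modified intention to treat". It makes no exception for safety, and it adds a per-protocol analysis of families who kept to their assigned sleeping arrangement. On method it says: "Chi-squared tests or Student t-tests will be used to compare the outcomes in the two groups". The one model it names, a discrete time model, is for breastfeeding.

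The outcomes concerned are primary. The Outcome measures section names these: "amount of time head covered, amount of time in thermal comfort zone, number of hypoxic events and amount of time in the sleep device", all taken from the overnight recording. On prognostic factors, the Randomisation section says: "As level of deprivation and parity may significantly affect the primary outcomes, stratified block allocations will be used". The Background adds: "Maternal smoking in pregnancy is recognised as the primary cause of increased vulnerability when bedsharing". Table 1 shows that smoking status is recorded in pregnancy.

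**The concern.** Two sections give different bases for the same primary outcomes, a third analysis set is added, and none of the three is ranked.

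Grouping babies by device used also gives up the randomisation, and with it the balance that stratification was meant to secure. If families who switch differ in deprivation or parity, and switch differently by arm, the comparison mixes device with family background. Chi-squared and t-tests do not correct for that.

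The direction matters here. The first hypothesis in Overall study design is that the wahakura does not differ significantly from the bassinet on thermal environment, head covering and desaturation. The Discussion wants the result to inform whether the device can be recommended as safe. Non-significance is therefore the favourable result, and a bias that hides harm would reassure wrongly.

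**Working it through.** **1. Reading the two rules together.** If the general rule governs, safety is analysed as randomised and the Contamination sentence is contradicted. If the specific rule governs, safety is analysed by device used only, since breastfeeding alone is given both analyses. The second reading is the more natural. It leaves a non-randomised comparison with no covariates or strata named.

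**2. What switching does with no confounding.** Assumptions: 100 babies per group (Total numbers required) and a share *s* switching in each arm. The effects come from the Sample size section: comfort zone 75% v 55%, head covering 3% v 18%. (The stated 98 per group for comfort zone reproduces with a continuity correction. The stated 88 for head covering exceeds the 78 I obtain, so it errs on the safe side and is not at issue here.)

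Randomised difference = true difference × (1 − 2*s*). For *s* = 5/10/20%:
- Comfort zone: 20 × 0.9/0.8/0.6 = 18/16/12 points.
- Head covering: 15 × 0.9/0.8/0.6 = 13.5/12/9 points.

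Simulation (40,000 trials, two-sided 5%):

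| Outcome | Power, device used | Power, randomised | Verdicts differ | Only device-used significant | Only randomised significant |
|---|---|---|---|---|---|
| Comfort zone | 85% at all three rates | 76/66/43% | 12/22/45% | 10/20/44% | about 2% |
| Head covering | 96% at all three rates | 91/83/56% | 6/15/41% | 6/14/41% | under 1% |

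Nearly all the disagreement is the device-used test finding a real harm that the diluted randomised test misses.

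**3. What confounded switching does.** All inputs are assumed except the prevalence. A factor is present in 53% (the Auckland smoking figure in the Background) and has a 0.5 SD effect on the outcome. True harm is 0.4 SD.

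Bias = 0.5 SD × (factor share among wahakura users − factor share among bassinet users).

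Worked case, one-way: families with the factor leave the wahakura at 30%, and everyone else switches at 10%.
- Wahakura users: with factor 0.53 × (0.7 + 0.1) = 0.424; without 0.47 × (0.9 + 0.1) = 0.470; share 0.424/0.894 = 0.474.
- Bassinet users: with factor 0.53 × (0.3 + 0.9) = 0.636; without 0.47 × (0.1 + 0.9) = 0.470; share 0.636/1.106 = 0.575.
- Gap −0.10, so bias = 0.5 × −0.10 = −0.05 SD.

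Simulation (20,000 trials), unadjusted device-used test against regression that includes the factor:

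| Switching | Bias (SD) | Type I error, unadjusted | Power, unadjusted | Power, adjusted |
|---|---|---|---|---|
| 20% in all groups | 0.00 | 5% | 78% | 80% |
| Factor leaves both devices at 30%, others 10% | 0.00 | 5% | 78% | 80% |
| One-way, 20% v 5% | −0.04 | 6% | 70% | 80% |
| One-way, 30% v 10% | −0.05 | 6% | 66% | 79% |
| Opposed, 30%/10% | −0.10 | 10% | 53% | 78% |
| Opposed, 40%/10% | −0.15 | 18% | 40% | 76% |

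Opposed means that families with the factor tend to leave the wahakura while those without it tend to leave the bassinet. Adjusted type I error stays near 5% throughout. With a 0.25 SD factor the bias halves: 0.02 SD one-way and 0.05 SD opposed, both at 30%/10%. Taking parity as the factor (assumed 40% first babies, 0.5 SD) gives the same one-way result: 0.05 SD, 6%, and 66% v 79% power.

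**4. Cross-check on a yes/no outcome.** Assume head-covering risk of 18% with the factor and 3% without, and no device effect, so bias = gap × 15 points. In the two one-way cases only the wahakura arm switches.
- One-way 20% v 5%: −0.076 × 15 = −1.1 points; 5.5% of tests reject.
- One-way 40% v 10%: −0.160 × 15 = −2.4 points; 7.4% reject.
- Opposed 40%/10%: −0.299 × 15 = −4.5 points; 17.4% reject.

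The randomised test stays at about 5%. These patterns flatter the wahakura; reversing them would reverse the sign.

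**The case against.** The strongest reply is that the plan has already chosen. A specific rule for three named outcomes normally overrides a general one, and the contrast with breastfeeding shows that the choice was deliberate. This largely stands. A reader might infer that a safety claim could rest on whichever analysis happens to be non-significant. The text does not support that, since its natural reading fixes device used in advance. What remains is that Data analysis makes no exception and leaves three sets unranked.

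A second reply is that the simulations favour the plan. This also stands for step 2: the frequent disagreement is a reason to keep analysis by device used, and does not show that it is unsafe. Even under opposed switching the unadjusted device-used test found the assumed harm more often than the randomised test did (53% v under 40%; 40% v 27%).

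A third reply is that the confounding is hypothetical. No section links deprivation, parity or smoking to switching. Smoking is tied to vulnerability when bedsharing and, tentatively, to arousal from hypoxia, so it is plausible for oxygen saturation but is not linked to head covering or temperature. That limits the size of the point without removing it: the plan itself says deprivation and parity may matter for these outcomes, and switching is by family choice.

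Last, covariate lists are commonly left to an analysis plan. A missing list alone would be no finding. Here the article itself fixes a non-randomised basis, names the tests, and states a conflicting general rule.

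**Conclusion.** The point holds in a limited form. The primary safety outcomes have two stated bases. On the more natural reading, the governing one is a non-randomised comparison with no named use of the two factors the plan calls prognostic.

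The bias cannot be sized from the document. It depends on assumed switching and an assumed 0.5 SD factor: nil when switching is unrelated to the factor or has the same pattern in both arms, about 0.05 SD under one-way switching at 30% v 10% (type I error 6%, power 66% against 79% adjusted), and 0.10 to 0.15 SD only under opposed switching, a pattern that nothing in the document suggests.

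The documents do not support the conclusion that analysis by device used is the wrong choice, or that the trial's safety result will be biased. Severity is minor to moderate.

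**What to change.** Keep device used as the lead safety analysis and add an exception to Data analysis, for example:

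*Except that oxygen saturation, head covering and peripheral temperature will be analysed primarily by the device in use at the sleep study, adjusted for deprivation (<3 v 3 or more), parity (1 v 2 or more) and smoking in pregnancy. The modified intention-to-treat result will be reported alongside, both with 95% confidence intervals; the per-protocol analysis is supportive only. If the device-used and randomised results disagree, this will be stated, and no safety claim will rest on the non-significant one.*

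If head covering is analysed as yes/no, events may be few (about 3 per 100 at the assumed 3%). Then use a method suited to sparse data that keeps the parity and deprivation strata, such as a Mantel-Haenszel risk difference. Stratifying by smoking alone would drop the two factors the plan names.

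The cost is a few sentences, since all three covariates are already collected. Adjustment costs no visible power: with 20% switching in all groups, three-covariate regression gave 79% against 77% unadjusted. Two downsides remain. Unmeasured confounding is not removed. If a significant result in either analysis counts as a warning, the false-alarm rate rises from 5% to about 7 to 9% for switching of 5 to 20%. The randomised result will also be weak if switching is common: at 20%, a 0.4 SD harm shrinks to 0.4 × 0.6 = 0.24 SD, with 37% power.
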